#### Within-session effect

At the beginning and end of each in-person intervention session, we collect a subset of PRO data with which to evaluate the effect of the session (Table 3). Each PRO measurement is collected from participants using a computer, a touch screen tablet, or a cell phone.

### Power calculations

Allowing for up to approximately 30% loss to follow-up, we plan to enroll 70 subjects per arm to retain 50 per arm per site. This drop-out rate is conservative, corresponding to criteria that we used previously to assess an intervention’s feasibility (38,116). We use a two-sample t-test 5% significance level (two-sided) as a conservative approximation to our analysis procedure. Due to additional covariate information and early information from subjects lost to follow-up, we expect greater power from our linear mixed model analysis.

To calculate effect size of the Aim 1 primary outcome measure: CIN sensation, we used the Numbness and Tingling (NT) 11-point scale (i.e., 0–10) from a study of physical activity for CIN among MBC survivors that observed post-chemotherapy scores with a standard deviation of 2.5 in the control arm and 1.9 in the treatment arm (Kleckner et al., 2018). Using the same standard deviations we have approximately 80% power to detect a minimum clinically significant difference of 1.25 (corresponding to minimally clinically important difference of 2.5 points on the 0–20 CIN-20 5-item sensory scale).

To calculate effect size of the Aim 2 primary outcome measure: dual-task function in the motor and cognitive domains, we used an effect size of 0.56 (Cohen’s *d*) based on preliminary data from 14 BC survivors with CIN participating in our pilot work (R21-AG068831); the effect size was verified as a conservative estimate as compared to a later calculation using a larger cohort of 46 BC survivors with CIN (17). Enrolling 70 participants per group (140 total) allows for a drop-out rate of up to 30% to yield full follow-up on 50 participants per arm and 80% power to detect the target effect size at the 5% significance level. This drop-out rate is conservative, corresponding to the criteria that we previously used to assess an intervention’s feasibility (38,116).

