### Study setting

The study is currently being conducted at The Ohio State University (OSU) in Columbus, Ohio (OH) and Yale Cancer Center in New Haven, Connecticut (CT). The research protocol has been approved by the OSU Institutional Review Board (IRB) and Yale has ceded review to this board as the single IRB for the multisite clinical trial. At OSU, participants are recruited from the Stephanie Spielman Comprehensive Breast Center (SSCBC) oncology practice as well as from the greater central OH community. At Yale, participants are recruited from the Yale Center for Breast Cancer (CBC) within the Smilow Cancer Center oncology hospital network as well as from the greater south central, CT and northern New York City, New York communities. Consent is obtained in a quiet and private setting prior to research activity either electronically, via REDCap (Research Electronic Data Capture, Nashville, TN), or using a paper version which is stored securely in a locked cabinet within a secure research-dedicated space at the host institutions. Assessments (i.e., screening, repeated baseline, midpoint, post intervention, and 1-month follow-up assessments) are performed in an outpatient care clinic setting or within the volunteer’s home environment, as preferred by the survivor. The EXP intervention is performed in a group setting of no more than 15 survivors at a time with their invited partners. The SOC portion of the CON intervention is performed by participants in their own home environment. Participants are compensated $20 per in-person assessment session that does not involve interventional instruction, with an additional $20 compensated for sessions that require sensors to be applied to the skin (potential total of up to $280 for participation in all assessments).

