### Statistical analysis

All outcome analyses will be performed on an intent-to-treat basis, and all hypothesis tests will be two-sided and at the 5% significance level or 95% confidence level. Longitudinal linear mixed models will be used to model changes in PROs and dual-task function. Fixed effects will be included for condition, session number within condition, baseline outcome measure, age, diabetes status, physical fitness activity (defined by weekly duration and metabolic equivalents), and number of previous chemotherapy lines. Random effects for subjects and study center will be used to account for within-subject and within-center correlation, and covariance estimated by restricted maximum likelihood. Exploratory Aim 3 will be assessed via causal mediation analysis using marginal structural models. The primary estimand will be the contrast representing the difference in mean change in outcome measure from baseline to week 4 (end of randomized treatment comparison) between treatment groups.

While we expect balance between groups due to randomization, we will adjust for potential confounders including age, body mass index, concurrent medications, and other variables if an imbalance between groups occurs by chance. Pearson’s *R* will be calculated to correlate PROs, functional outcomes, biomechanical outcomes, brain activity, and biomarker outcomes. We use a longitudinal mixed effect model to analyze all outcomes and do not impute missing outcomes. Subjects will be analyzed in the group to which they were randomized regardless of compliance with the assigned intervention. We will evaluate the effect of the number of intervention sessions completed on outcomes.

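### The sample-size section gives two incompatible retention targets, and neither the power calculation nor the stated mixed model allows for Tango being delivered in classes

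*Protocol article*

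**What the plan says.** The Power calculations section gives the target twice. It opens with "we plan to enroll 70 subjects per arm to retain 50 per arm per site". Further down it says "Enrolling 70 participants per group (140 total) allows for a drop-out rate of up to 30" per cent, "to yield full follow-up on 50 participants per arm and 80% power to detect the target effect size", with no mention of site. Study setting names two sites: "The study is currently being conducted at The Ohio State University (OSU) in Columbus, Ohio (OH) and Yale Cancer Center in New Haven".

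Power comes from a two-sided 5% two-sample t-test, which the section calls conservative. It gives two reasons: extra covariate information, and "early information from subjects lost to follow-up, we expect greater power from our linear mixed model analysis".

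On delivery, Study setting says "The EXP intervention is performed in a group setting of no more than 15 survivors at a time with their invited partners", whereas the four weeks of standard of care take place in each participant's own home. Statistical analysis names the random structure: "Random effects for subjects and study center will be used to account for within-subject and within-center correlation". Class appears in neither the power calculation nor the model.

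**The concern.** There are two separate matters.

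The first is arithmetic. The opening target cannot be met from the stated enrolment, and it disagrees with the later sentence in the same section. It stands in the sentence that defines the size of the trial.

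The second is a missing level of variation. Participants in one Tango class share an instructor, a room, partners and a social setting, and the Discussion counts that setting among the reasons the intervention should work. Outcomes may therefore correlate within class in the Tango arm, with no counterpart in the control arm before week 4 (a partially nested design). A center effect with two levels cannot represent several classes within a center. If the correlation is positive, the primary confidence intervals are too narrow and the true type I error exceeds 5%. The word conservative also takes account only of influences that raise power.

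**Working it through.** **Inputs from the protocol article.** 70 enrolled per arm, loss up to about 30%, two-sided 5%, 1:1 allocation, two sites. Aim 1: SDs 2.5 (control) and 1.9 (treatment), difference 1.25. Aim 2: d = 0.56. Class size at most 15.

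**Inputs assumed, because the documents give none.** Within-class ICC 0.02 to 0.05, and m = 5 to 10 Tango-arm participants per class.

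**1. Retention.**
- 50 × 2 sites = 100 completers per arm, more than the 70 enrolled.
- Keeping 100 at 30% loss would need 100/0.70 = 143 per arm, or 286 in total, against the stated 140.
- 70 × 0.70 = 49. Keeping 50 of 70 is a loss of 1 − 50/70 = 28.6%.

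**2. The stated 80%.** Aim 1 SD = √((2.5² + 1.9²)/2) = √4.93 = 2.22, so d = 1.25/2.22 = 0.563. At 50 per arm the non-centrality is 1.25/√(9.86/50) = 2.815 for Aim 1 and 0.56 × √25 = 2.80 for Aim 2. Power by non-central t:

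| Completers per arm | Aim 1 | Aim 2 |
|---|---|---|
| 49 | 78.8% | 78.4% |
| 50 | 79.6% | 79.2% |
| 100 | 97.7% | 97.6% |

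The plan's figure reproduces at 50 per arm overall and not at 50 per arm per site.

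**3. Class clustering, Tango arm only, 49 completers per arm (normal approximation).**
- Design effect: DE = 1 + (m − 1) × ICC.
- True SE = √((SD_C² + SD_E² × DE)/n). Naive SE is the same with DE = 1.
- Power = Φ(δ/true SE − 1.96).
- Type I error if class is ignored = 2[1 − Φ(1.96 × naive SE/true SE)].

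Worked case, Aim 1, m = 10, ICC 0.05: DE = 1.45. True SE = √((6.25 + 3.61 × 1.45)/49) = 0.484. Power = Φ(1.25/0.484 − 1.96) = Φ(0.62) = 73.3%. The SE ratio is 0.4486/0.4841 = 0.927, so type I error = 2[1 − Φ(1.816)] = 6.9%.

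| m | ICC | DE | Power, Aim 1 / Aim 2 | Type I error if class ignored |
|---|---|---|---|---|
| 5 | 0.02 | 1.08 | 78.4% / 77.6% | 5.3% / 5.5% |
| 5 | 0.05 | 1.20 | 76.7% / 75.3% | 5.9% / 6.2% |
| 10 | 0.02 | 1.18 | 77.0% / 75.6% | 5.8% / 6.0% |
| 10 | 0.05 | 1.45 | 73.3% / 70.7% | 6.9% / 7.7% |

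On this approximation the unclustered figures at 49 per arm are 79.6% and 79.2%. The ratio of naive to true SE runs from √(9.86/(6.25 + 3.61 × 1.08)) = 0.986 to √(2/2.45) = 0.904.

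**4. Offset from baseline adjustment.** An assumed baseline–outcome correlation r multiplies the SE by √(1 − r²).
- r = 0.5, m = 10, ICC 0.05, 49 per arm: 84.6% (Aim 1) and 82.4% (Aim 2).
- r = 0.3, m = 8, ICC 0.05, 50 per arm: 79.3% and 77.3%.

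The ratio of naive to true SE, and so the type I error, does not change, because the factor cancels.

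**5. The early-information argument.** In Tables 1 and 2 TUG-Cog is assessed at baseline and week 4, with nothing between, and Table 3 does not list it. Baseline enters the model as a covariate, so a participant lost before week 4 adds no TUG-Cog outcome. Numbness/tingling is collected weekly or at each session, so the argument can apply there.

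**The case against.** The strongest reply is that little of substance is at stake. The section resolves its own slip by giving 140 in total and 50 per arm, and the 80% confirms which number was used. That stands: a reader might infer a real twofold doubt about the target, and the documents do not support it. Nor is 49 against 50 an error, since the loss is stated as approximately 30%.

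On clustering, the reply is that no ICC is given and 15 is a ceiling. Trial status puts enrolment from January 2025 to December 2028, about 47 months. Seventy Tango participants over two sites is 70/47/2 = 0.74 per site per month, or about 1.4 per 8-week course (about 1.84 months). Even the upper pace under Adequacy of the potential participant pool, 10 enrolled per month across sites, gives 2.5 × 1.84 = about 5 Tango-arm participants per site per course. Classes may be small unless recruitment is batched, and small classes with a low ICC cost only a few points. This also stands, and it is why m = 10 is an upper assumption here and not an expectation.

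A reader might also infer that the trial fails to deliver 80% power. The documents do not support that either. The plan adjusts for baseline, and step 4 shows that net power could fall on either side of 80%.

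Finally, class could be handled in a fuller analysis plan. However, the article does state its random effects, and the level at which treatment is delivered is not among them. Covariate gain does not answer that.

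**Conclusion.** The retention target is wrong as written. It is a wording error: the governing figure is about 50 completers per arm across both sites, with unadjusted t-test power of about 78% to 80%.

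The omission of class is a genuine gap in the stated model. Its size is conditional. With ICC 0.02 to 0.05 and 5 to 10 Tango participants per class, both assumed, standard errors are about 1% to 10% too small, true type I error is about 5.3% to 7.7%, and unadjusted power is about 71% to 78%. With an ICC of zero there is no effect. Whether power after baseline adjustment exceeds 80% cannot be settled from the documents, so describing the t-test as conservative is unproven, not refuted. The early-information argument does not apply to TUG-Cog.

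**What to change.** - Delete *per site* and state one target: 140 enrolled, 70 per arm across both sites, about 50 retained per arm (49 at exactly 30% loss).
- Record the class of each Tango-arm participant from now on, and define class in advance in case classes run continuously or include controls who have crossed over.
- Add a class random effect in the Tango arm only (partially nested model). Use a small-sample degrees-of-freedom correction such as Kenward–Roger, because classes may be few: 49 completers at 10 per class is about five.
- Report power over a stated range of ICC and class size, together with the expected gain from covariates. Keep the word conservative only if that net calculation supports it.
- Limit the early-information argument to the symptom score.

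The cost is some wording, one recorded variable and one model term. Intervals may be slightly wider and the stated power less favourable. No extra patients are needed. Enrolment is already open, and class membership is easier to record as it happens than to reconstruct.

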### Randomization

After a participant has qualified, consented to participate in this trial, and completed repeated baseline testing, researchers randomize them 1:1 into one of two groups: EXP or CON. Randomization is blocked and stratified by site, age (≥61 vs <61), baseline CIN sensation (Likert ≥4 vs <4), and baseline functional status (TUG-Cog ≥12.64 s vs <12.64 s) based on the results of previous work in our lab (17). CIN sensation was identified through the 11-point Likert scale (59) administered during the repeated baseline period. Functional status is identified by averaging the times of 3 TUG-Cog trials that participants completed during the repeated baseline period.

Randomization is accomplished using a schedule that was generated by the statistician prior to the trial opening to enrollment. The clinical research coordinator will assign allocation and enroll participants. One member of the research team is blinded to the randomization schedule prior to allocation; this researcher administers TUG and TUG-Cog to participants throughout the study. Study participants cannot be blinded; they will inevitably know their group assignment as they are participating in a distinct intervention in comparison to usual care.

### Data management

Each study participant is assigned a unique six-digit identification number that cannot be traced to their protected health information. Participant data, coded using these identification numbers, are stored in a central database using REDCap. REDCap is a secure web-based platform that is designed for clinical trials which meets both HIPAA and 21 CFR. Clinical and biomechanical data are collected by study staff who input results into REDCap manually or via data upload. PRO data is manually entered into REDCap by study participants: participants undergoing the Tango intervention fill out questionnaires within REDCap before the start and at the end of each Tango session. SOC participants fill out questionnaires within MyCap, a mobile device application of REDCap once per week during the SOC wit period, for the purpose of adverse events reporting and symptoms tracking, then transition into the Tango intervention protocol in which they fill out questionnaires within REDCap before the start and end of each Tango session.

### Statistical analysis

All outcome analyses will be performed on an intent-to-treat basis, and all hypothesis tests will be two-sided and at the 5% significance level or 95% confidence level. Longitudinal linear mixed models will be used to model changes in PROs and dual-task function. Fixed effects will be included for condition, session number within condition, baseline outcome measure, age, diabetes status, physical fitness activity (defined by weekly duration and metabolic equivalents), and number of previous chemotherapy lines. Random effects for subjects and study center will be used to account for within-subject and within-center correlation, and covariance estimated by restricted maximum likelihood. Exploratory Aim 3 will be assessed via causal mediation analysis using marginal structural models. The primary estimand will be the contrast representing the difference in mean change in outcome measure from baseline to week 4 (end of randomized treatment comparison) between treatment groups.

While we expect balance between groups due to randomization, we will adjust for potential confounders including age, body mass index, concurrent medications, and other variables if an imbalance between groups occurs by chance. Pearson’s *R* will be calculated to correlate PROs, functional outcomes, biomechanical outcomes, brain activity, and biomarker outcomes. We use a longitudinal mixed effect model to analyze all outcomes and do not impute missing outcomes. Subjects will be analyzed in the group to which they were randomized regardless of compliance with the assigned intervention. We will evaluate the effect of the number of intervention sessions completed on outcomes.

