## Figures and Tables

**Figure 1 F1:**
[figure not shown]
Flow chart of study design from screening through the follow-up (f/u) period with assessments indicated throughout. Postural control data will be taken at each Tango session in addition to all assessment periods. Each assessment timepoint may contain 1) clinical measures: PROs, dual-task function, and upper extremity function; 2) biomechanical measures: postural control and gait stability; and 3) exploratory measures: biomarker and EEG sampling. For more detailed information, refer to tables 1 & 2. Processing of data will happen after the conclusion of the follow-up period per participant. Analysis of the primary outcome measures will be conducted after all data has been collected.

**Table 1 T1:** SPIRIT report of intervention effect outcome measures for EXP group.

	Study Period						
	Enrollment		Allocation	Post-Allocation			
Timepoints	3 + months post-last taxane exposure	Baseline	0	EXP 4 weeks (Tango midpoint)	EXP 8 weeks (Tango end)	EXP 12 weeks (1-month follow up)	6-month follow up period, assessed weekly
ENROLLMENT:							
Eligibility screen	x						
Informed consent	x						
Allocation			x				
ASSESSMENTS:							
Adverse events (including falls)		x^†^		x	x	x	x
Neuropathy (primary outcome Aim 1)		x^†^		x	x	x	x
TUG-Cog (primary outcome Aim 2)		x		x	x	x	
CTCAE		x^†^		x	x	x	
Pain		x^†^		x	x	x	
Fatigue		x^†^		x	x	x	
GAD-2		x		x	x	x	
PHQ-2		x		x	x	x	
SF-36		x		x	x	x	
Satisfaction with intervention				x	x		
Activity outside of study tracking		x^†^		x	x	x	x
Intrinsic motivation				x	x		
Postural control during silence (QEC)		x^†^		x	x	x	
Postural control during music listening (QECm)		x^†^		x	x	x	
TUG		x		x	x	x	
TNSr+		x		x	x	x	
MiniBEST		x			x		
6mwt (EMG, IMUs)		x			x		
Upper extremity function		x		x	x	x	
Goal attainment (COPM)		x			x	x	
Blood-based biomarkers		x			x		
Cognitive load (EEG)		x		x	x	x	

† indicates a measure was repeated 3 times

**Table 2 T2:** SPIRIT report of intervention effect outcome measures for CON group.

	Study Period							
	Enrollment		Allocation	Post-Allocation				
Timepoints	3 + months post-last taxane exposure	Baseline	0	CON 4 weeks (post-SOC)	CON 8 weeks (Tango midpoint)	CON 12 weeks (Tango end)	CON 16 weeks (1-month follow up)	6-month follow-up period, assessed weekly
ENROLLMENT:								
Eligibility screen	x							
Informed consent	x							
Allocation			x					
ASSESSMENTS:								
Adverse events (including falls)		x^†^		x	x	x	x	x

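### With only two sites, center is fitted as a random effect, and each primary model omits one stratification baseline: a low-cost improvement to the analysis model, not a fault in its validity

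*Protocol article*

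**What the plan says.** Study setting names two sites: "The study is currently being conducted at The Ohio State University (OSU) in Columbus, Ohio (OH) and Yale Cancer Center in New Haven".

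Randomization states: "Randomization is blocked and stratified by site, age (≥61 vs <61), baseline CIN sensation (Likert ≥4 vs <4), and baseline functional status". The last factor is TUG-Cog, cut at 12.64 s.

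Statistical analysis gives the model: "Fixed effects will be included for condition, session number within condition, baseline outcome measure, age, diabetes status", then physical fitness activity and number of previous chemotherapy lines. For center it states: "Random effects for subjects and study center will be used to account for within-subject and within-center correlation", with "covariance estimated by restricted maximum likelihood". Age, body mass index, concurrent medications and other variables may be adjusted for if the arms turn out unbalanced.

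Power calculations uses an unadjusted two-sample t-test as a conservative stand-in for this model. It expects the mixed model to do better, partly because of its covariates.

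**The concern.** Two features of the model do not follow the randomisation scheme.

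1. **Center.** A variance component needs a reasonable number of units, and here there are two. The estimate is very unstable and often exactly zero. When it is zero, site has in effect left the model, although allocation was stratified by it.

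2. **Baselines.** Both sensation and TUG-Cog at baseline were chosen as stratification factors, but the fixed effects carry only the baseline of the outcome being analysed. The other one is missing from each primary model. The chance-imbalance provision is unlikely to bring it back, because stratification exists to prevent imbalance in exactly these factors.

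At stake is some precision, in a trial whose stated power is 80% with no margin, and a model whose content is not fully settled before the data are seen.

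**Working it through.** **Which factors each primary model contains**

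| Stratification factor | Sensation model | TUG-Cog model |
|---|---|---|
| Site | random effect | random effect |
| Age | fixed | fixed |
| Baseline sensation | fixed (own baseline) | absent |
| Baseline TUG-Cog | absent | fixed (own baseline) |

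Three of the four factors are present in each model, and one is absent.

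**The plan's own power figure.** Inputs from Power calculations: 50 followed per arm, two-sided 5%; Aim 1 difference 1.25 with SDs 2.5 and 1.9; Aim 2 d = 0.56.

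- Aim 1: SD = √((2.5² + 1.9²)/2) = 2.22, so d = 1.25/2.22 = 0.563.
- Noncentral t with 98 df and noncentrality d√(50/2): power is 79.6% for Aim 1 and 79.2% for Aim 2. The normal approximation gives 80.4% and 80.0%.

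The stated 80% is reproduced for both aims.

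**Center variance from two sites.** Assumptions: 50 completers per site (the protocol gives no split of the 100), one observation per person, residual variance 1 and site variance τ². The REML estimate is max(0, (MSB − MSW)/50), and MSB is distributed as (1 + 50τ²) times a chi-square on 1 df. Taking MSW as 1,

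P(estimate = 0) = P(χ²₁ < 1/(1 + 50τ²)).

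| Site SD (residual SDs, assumed) | 1/(1 + 50τ²) | P(estimate = 0) |
|---|---|---|
| 0 | 1 | 68% |
| 0.1 | 1/1.5 | 59% |
| 0.2 | 1/3 | 44% |
| 0.3 | 1/5.5 | 33% |

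The estimate is also poor when it is not zero. At an intraclass correlation of 0.05 (true variance 0.053), its 2.5th to 97.5th percentiles run from 0 to 0.34.

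**Effect of the random center on the treatment contrast.** Treatment standard error with 100 participants, random center (generalised least squares, τ² from 0 to 0.25) against fixed site:

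- 25 per arm at each site: 0.200 under both, identical.
- Splits of 27/23 and 23/27, or 22/28 and 28/22: the random-center standard error is 0.02% to 0.7% smaller.

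So the random effect does not itself lose precision.

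**Effect of the omitted baseline.** Let r be the partial correlation of the omitted baseline with the outcome, given the covariates already in the model. The standard error is multiplied by √(1 − r²) and the standardised effect becomes d/√(1 − r²). The protocol gives no value for r, so a range is shown. The unadjusted t-test power is only an illustrative starting point.

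| r (assumed) | Reduction in SE | Aim 1 power (from 79.6%) | Aim 2 power (from 79.2%) |
|---|---|---|---|
| 0.1 | 0.5% | 80.0% | 79.6% |
| 0.2 | 2.0% | 81.2% | 80.8% |
| 0.3 | 4.6% | 83.2% | 82.8% |
| 0.4 | 8.3% | 86.0% | 85.7% |

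**The case against.** The strongest reply is that nothing here threatens the trial's conclusions. Allocation is stratified by site, so treatment is compared within site, and the treatment standard error hardly changes whether center is random, fixed or estimated away. REML gives zero only when the observed site difference is small. The gain from the extra baseline rests on a correlation found nowhere in the protocol, and at r = 0.1 it is only 0.4 percentage points. The 80% starting figure comes from an unadjusted test, so the resulting powers do not describe the planned mixed model. All of this stands, and it limits the point to an improvement.

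A reader might infer more from the text, in three ways that it does not support:

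- **That the model drops the stratification factors generally.** It does not. Age and the outcome's own baseline are fixed effects, and site is nominally present.
- **That the random center wastes power or makes the primary models fail to converge.** The standard-error comparison shows no loss. A variance estimate of zero is a boundary solution, not a failed fit, and convergence failure has not been shown.
- **That the type I error rate is inflated.** Leaving out a prognostic stratification factor tends to make the standard error too large for the design, so the test errs on the conservative side.

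The reply does not remove the two mismatches. The model is stated explicitly, so this is not a detail left to an unseen analysis plan. The protocol also looks to covariates for power beyond the t-test, and omitting a baseline judged important enough to stratify on works against that.

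**Conclusion.** The point holds as a free improvement. A random effect for two centers cannot estimate between-center variation usefully. It leaves the presence of site in the model to the data: a zero estimate in about 68% of trials if the sites do not differ and 44% at a site SD of 0.2, assuming 50 completers per site. Each primary model lacks exactly one stratification factor, the other primary outcome's baseline.

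The consequence is a slightly conservative test and some forgone precision, all of it from the omitted baseline. The gain from restoring it runs from negligible at r = 0.1 to about 6 percentage points of power at r = 0.4. The actual r is unknown. The estimand, the nominal error rate and the stated sample size are unaffected.

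**What to change.** In both primary models, replace the random center effect with a fixed site effect and keep the random subject effect. Include baseline sensation and baseline TUG-Cog as continuous covariates in both models, along with age. All four stratification factors are then in each model in advance, and none depends on a variance estimate or on an observed imbalance. How the repeated baseline sensation scores are summarised can stay with the analysis plan, provided the same summary is used in both models.

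The cost is about two degrees of freedom per model (one for site, one for the added baseline) and a change of wording. Site is known, and both baselines are already collected before randomisation in order to stratify. Trial status puts the end of enrollment at December 2028, and the Figure 1 caption places the primary analysis after all data are collected, so the change can be made well before any outcome comparison.
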